# 1. Background

*Soil-Transmitted Helminths*

The three major Soil-Transmitted Helminths (STH), *Ascaris lumbricoides* (roundworm)*, Trichuris trichiura* (whipworm) and *Necator americanus/Ancylostoma duodenale* (hookworms) are amongst the most widespread parasites worldwide. An estimated 4.5 billion individuals are at risk of STH infection and more than one billion individuals are thought to be infected, of whom 450 million suffer morbidity from their infection, the majority of who are children. An additional 44 million infected pregnant women suffer significant morbidity and mortality due to hookworm-associated anemia. Approximately 135,000 deaths occur per year, mainly due to infections with hookworms or *A. lumbricoides* (Bundy *et al*., 1992; Stoltzfus *et al*., 1996; Crompton *et al*., 2002; WHO, 2005; Bethony *et al*., 2006)*.*

*Treatment and monitoring efficacy*

The periodic administration of anthelmintics is currently the most widely used method to control these infections. Rather than aiming to achieve eradication, these control programs are focused on reducing infection intensity and transmission potential, primarily to reduce morbidity. The benzimidazole (BZ) drugs, i.e. albendazole (ALB) and mebendazole (MBZ), are the most widely used drugs and a scale-up of these large-scale treatment programs underway in various parts of across Africa, Asia and Latin-America (donation of 400 million tablets of albendazole by GlaxonSmithKline and 200 million tablets of mebendazole by Johnson & Johnson). Due to the scarcity of available anthelmintics, it is imperative that monitoring systems are designed both to assess progress and to detect any changes in therapeutic efficacy that may arise from the selection of worms carrying genes responsible for drug resistance. Although some small-scale studies (De Clercq *et al*., 1997; Albonico *et al*., 2004) have suggested a reduced efficacy of these components, these studies should be interpreted with some caution. Published studies are confounded by methodological variations including treatment regimens, poor quality of drugs, differing statistical analyses used to calculate therapeutic efficacy, as well as a range of other problems in study design, such as small sample size, diagnostic methods, variation in pre-intervention infection intensities and confounding factors related to geographical locations. A recent multinational trial standardized across different endemic regions using a protocol which was standardized in terms of the treatment (a single-oral 400mg dose of ALB originating from the same batch), the follow up (between 14 and 30 days after) and the detection technique (the McMaster egg counting technique), indicated that ALB is highly efficacious against *A. lumbricoides* and hookworms, but not for *T. trichiura* (Vercruysse *et al*., 2011). MBZ is likely to be more efficacious against *T. trichiura*, yet reliable efficacy data for this BZ are not available.

# 2. Objectives

The overall objective is to monitor efficacy of MBZ against STH.

The primary objective is:

(1) to monitor the efficacy a single dose 500 mg of MBZ against STH infections by means of Faecal Egg Count Reduction (FECR) and Cure Rate (CR).

# 3. Materials and Methods

## 3.1. Study sites and population

**Study sites**

Six out of the seven study sites involved in the 2009 Study (ALB) confirmed their participation, including Brazil (Minas Gerais State), Cambodia (Phnom Phem), Cameroon (Yaoundé), Ethiopia (Jimma), Tanzania (Pemba Island) and Vietnam (Hanoi). India will be replaced by Argentina (Orean region). Each of these study sites has a documented history of STH and drug selection pressure. Moreover, each of them has well equipped diagnostic facilities, skilled personnel.

**Study Population**

Schoolchildren between 4 and 18 years old are the focus of this study because of two main reasons: School children are normally a major target for regular treatment with anthelminthic, because they are the group that usually has the heaviest worm burdens for *A. lumbricoides* and *T. trichiura*, and are steadily acquiring hookworm infections. In addition, they are in a period of intense physical and intellectual growth (Bundy *et al.,* 1992; Crompton and Nesheim, 2002). Deworming schoolchildren has a considerable benefit on their nutritional status (Stoltzfus *et al*., 1996, Curtale *et al.,* 1995), physical fitness, appetite, growth (Stephenson *et al*., 1993) and intellectual development (Nokes *et al* 1994).

## Study design

**Primary objective**

Following obtaining informed consent, schoolchildren in the target age range group will be recruited and asked to provide a recent stool sample (an interval of less than 4 hours) that will be processed to determine the FEC for each STH present. For the initial sampling the aim is to enroll at least 250 infected children for at least one of the STH. This sample size was selected based on statistical analysis of study power, using random simulations of correlated over-dispersed FEC data reflecting the variance-covariance structure in a selection of real FEC data sets. This analysis suggested that a sample size of up to 200 individuals (α = 0.05, power = 80%) was required to detect a 10 percentage point drop from a null efficacy of ~ 80% (mean percentage FEC ∆ per individual) over a wide range of infection scenarios. Standard power analyses for proportions also indicated that the detection of a ~10 percentage point drop from a null cure rate required sample sizes up to 200 (the largest samples being required to detect departures from null efficacies of around 50%). Given an anticipated non-compliance rate of 25%, a sample of 250 infected subjects was therefore considered necessary at each study site.

All children providing stool samples will be treated with MBZ single table of 500mg under supervision (chewing + water). The MBZ will be provided (free) by the coordinating group. **Seven up to fourteen days (maximum interval)** after treatment a second faecal sample will be collected from the children to determine again FEC. Subjects who are unable to provide a stool sample at follow-up, or who are experiencing a severe concurrent medical condition or have diarrhea at time of the first sampling, will be excluded from the study.

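### The 250 per site counts children with any STH and sets no minimum per species, so the stated 80% power is not secured for a given species at a site

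*Protocol*

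**What the plan says.** Under Study design, Primary objective, the protocol gives two power arguments. For egg count reduction, simulation indicated that "a sample size of up to 200 individuals (α = 0.05, power = 80%) was required" in order "to detect a 10 percentage point drop from a null efficacy of ~ 80% (mean percentage FEC ∆ per individual"). For cure, "the detection of a ~10 percentage point drop from a null cure rate required sample sizes up to 200", with "the largest samples being required to detect departures from null efficacies of around 50"%.

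The enrolment target follows: "Given an anticipated non-compliance rate of 25%, a sample of 250 infected subjects was therefore considered necessary at each study site". The unit being counted is defined a few lines earlier: "For the initial sampling the aim is to enroll at least 250 infected children for at least one of the STH".

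Measurement is by species. Each child gives a stool sample "that will be processed to determine the FEC for each STH present", and Parasitological techniques names three targets: *A. lumbricoides*, *T. trichiura* and hookworms. Section 1 (Background) discusses efficacy by species: the earlier multinational trial "indicated that ALB is highly efficacious against" two of these parasites but not against *T. trichiura*, where mebendazole is expected to do better.

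Section 2 states the objective for STH infections in general, by egg count reduction and cure rate. Section 3.4 refers to the cited albendazole trial for the analysis and states no denominators.

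**The concern.** A child without hookworm at baseline contributes nothing to a hookworm cure rate or a hookworm egg count reduction. The sample needed for one estimate is therefore a number of children carrying that species. The recruitment target can be met by children carrying any of the three, in any mix, so a site can reach 250 with few carriers of one parasite while the protocol still reads as offering 80% power there.

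The protocol itself lists small samples among the weaknesses of earlier efficacy studies. The number recruited is also fixed by this document, and a later analysis plan cannot supply carriers who were not enrolled.

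**Working it through.** **Inputs from the protocol (Study design, Primary objective).** α = 0.05; power 80%; a 10-point drop; worst-case null cure rate about 50%; null egg count efficacy about 80%; non-compliance 25%; 250 enrolled per site.

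**Assumptions.** Two-sided test (not stated). Share *s* of enrolled children carrying a species: 70, 50 and 30% (the protocol gives no value).

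**Step 1: reproduce the 200.** For a one-sample test of a proportion,

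n = [1.96·√(p0(1−p0)) + 0.842·√(p1(1−p1))]² / (p0−p1)².

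- p0 = 0.50, p1 = 0.40: n = 194
- p0 = 0.80, p1 = 0.70: n = 137
- p0 = 0.90, p1 = 0.80: n = 86

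The largest value over the null rates tried is 195, at p0 = 0.55. This agrees with a maximum of 200 reached near 50%. A one-sided test gives 153 and a two-sample comparison 388 per group, so the basis appears to be one-sample and two-sided. The egg count simulation cannot be reproduced, because its variance inputs are not given.

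**Step 2: from 200 to 250.** 200 × 1.25 = 250, whereas 200 / 0.75 = 267. With 25% lost, 250 × 0.75 = 187.5 remain.

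**Step 3: evaluable carriers and power.** Evaluable n = 250 × 0.75 × s. Power for a 10-point drop = Φ{[0.1·√n − 1.96·√(p0(1−p0))] / √(p1(1−p1))}. For example, with n = 94 and p0 = 0.50: Φ[(0.970 − 0.980)/0.490] = Φ(−0.02) = 49%.

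| Share s | Evaluable n | Null 50% | Null 80% | Null 90% | Detectable drop at 80% power, null 50% |
|---|---|---|---|---|---|
| 100% | 187 | 79% | 90% | 97% | 10.2 points |
| 70% | 131 | 63% | 78% | 92% | 12.1 points |
| 50% | 94 | 49% | 66% | 83% | 14.3 points |
| 30% | 56 | 32% | 47% | 66% | 18.3 points |

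**Step 4: share needed for 80% power at a site.** Required n / 187.5:

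- null 50%: 194/187.5 = 103%, not attainable at the minimum enrolment
- null 80%: 137/187.5 = 73%
- null 90%: 86/187.5 = 46%

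**Step 5: egg count reduction.** If 200 children give exactly 80% power for a 10-point drop, the implied SD is 10·√200 / (1.96 + 0.842) = 50.5 points. Power = Φ(10·√n/50.5 − 1.96) is then about 77% at s = 100%, 48% at 50% and 32% at 30%, close to the worst-case cure column.

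**Step 6: separate the two causes.** With 200 evaluable children when all carry the species, the shares alone would leave 140, 100 and 60. Multiplying by 187.5/200 gives the 131, 94 and 56 above. The species mix causes most of the loss at these shares; the 25% allowance adds a smaller part.

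**Step 7: sites combined.** At a 30% share, 7 × 56 = 392 children give about 98% power at the 50% null, ignoring variation between sites.

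**The case against.** The strongest reply has four parts.

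1. **The enrolment sentence is ambiguous.** It could mean that for at least one species a site should have 250 infected children. That stands as a possible reading. It would protect one species per site and leave the other two without a minimum, so the point survives in reduced form.

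2. **Species-specific denominators are inferred.** Section 2 speaks of STH infections together, and Section 3.4 defers to a paper that is not at hand. This is correct. The inference rests on separate egg counts for each parasite and on a Background that asks about efficacy by species, a question an any-STH result could not answer.

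3. **The 200 is a maximum and the 250 a minimum.** Also correct. At a 90% null, a species carried by half the children has about 83% power. The Background says, however, that reliable mebendazole data for *T. trichiura* are lacking, so a high null cannot be presumed for that species.

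4. **The objective is to monitor efficacy, and the seven sites combined give ample numbers.** This stands for combined results. The protocol sets its sample size for each site, though, and that is the level at which its power statement is read.

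A reader might infer that most species-by-site results are underpowered, that the stated power holds only for a species nearly every child carries, or that a real loss of efficacy would usually be missed. The documents support none of these. The first needs a species mix that they do not give. The second fails at nulls of 80% and 90%, where shares of 73% and 46% suffice. The third fails even at the 50% null with a 70% share, where power is 63%.

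**Conclusion.** The concern holds in a limited form. The protocol attaches 80% power to a per-site number that is not a number of carriers of any given species. On either reading of the enrolment sentence at least two species have no minimum, so the power is not secured for them at a site.

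The size of the shortfall depends on two unknowns, the species share and the null efficacy. Over the assumed shares of 70 to 30%, power runs from 63 to 32% in the protocol's worst case and from 92 to 66% at a null cure rate of 90%. The figures rest on a two-sided one-sample test, loss of exactly 25%, enrolment at the minimum of 250, and species-specific denominators. The part due to the 25% allowance is a separate matter: it takes worst-case power to about 79% with no dilution by species. Results for the seven sites combined are not in question.

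**What to change.** State whether the 250 is a count per species or of children with any STH.

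If it is per species, name the species to which it applies at each site, and note that 250 with 25% lost leaves about 187 evaluable; keeping 200 takes 267.

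If it is any STH:

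- Replace the power sentence with a table of evaluable n, power and detectable drop by species share and null efficacy, along the lines of the table above.
- State that 80% power applies at a site only to species whose evaluable number reaches what the relevant null requires: about 194 at 50%, 137 at 80% and 86 at 90%. A flat cut-off of 200 would not work, because at minimum enrolment with 25% lost every species at every site falls below it.
- Report the remaining species-by-site results as estimates with confidence intervals.
- Base species-level conclusions on the seven sites combined, stratified by site.

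Prevalences from the 2009 study could inform the shares for six sites, but not for Argentina, which replaces India.

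The any-STH option costs protocol wording and one table, with no extra children. Its downside is weaker site-level claims for the less common species. Keeping 200 evaluable carriers at every site instead would take 200/0.75/0.5 = 534 any-STH positives at a 50% share and 889 at 30%.

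### The 250-per-site target applies the 25% loss allowance the wrong way: at that loss it leaves about 187 evaluable children, slightly below the stated worst-case 200 (minor)

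*Protocol*

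**What the plan says.** All of the material is in the Protocol, Study design, under Primary objective. For egg count reduction, simulations suggested that "a sample size of up to 200 individuals (α = 0.05, power = 80%) was required" to detect a fall of 10 percentage points from a null efficacy of about 80%. For cure rate, standard calculations for proportions gave the same ceiling for a fall of about 10 points: "percentage point drop from a null cure rate required sample sizes up to 200", with "the largest samples being required to detect departures from null efficacies of around 50" per cent. The conclusion is then drawn: "Given an anticipated non-compliance rate of 25%, a sample of 250 infected subjects was therefore considered necessary at each study site".

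Two other statements in the section bear on this. The enrolment aim is worded as a minimum of 250 children infected with at least one of the helminths. Children who cannot give a stool sample at follow-up are excluded from the study.

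**The concern.** The protocol presents 250 as a consequence of two inputs, up to 200 individuals and 25% non-compliance, and it gives no other basis for the figure. A non-compliance rate is ordinarily a fraction of those enrolled, so the allowance should be made by dividing by the fraction retained. The 250 comes out exactly only if 25% is added to 200. Treatment is supervised and children without a follow-up stool drop out of the analysis, so the loss directly reduces the evaluable number.

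What is at stake is whether the only sample-size justification in the protocol, which applies at each study site, delivers the number it says it needs in the least favourable scenario.

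**Working it through.** **Inputs, all from Study design, Primary objective**
- Evaluable children needed, worst case: 200 (stated as a ceiling, for both endpoints).
- Anticipated non-compliance: 25%.
- Enrolment target: 250 per site.
- Alpha 0.05 and power 80%, stated for the egg-count simulation. Sidedness is not stated. The cure-rate sentence names no alpha, power or test.

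**Step 1. Reproduce the 250**
- Dividing by the fraction retained: 200/(1 - 0.25) = 266.7, rounded up to 267. This is not 250.
- Adding the percentage: 200 x (1 + 0.25) = 250. This matches exactly.

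**Step 2. Run the target forward**
- 250 x (1 - 0.25) = 187.5, so about 187 evaluable.
- Shortfall against 200: 12.5, that is 12 to 13 children, or 12.5/200 = about 6%.
- Loss at which 250 still leaves 200: 1 - 200/250 = 20%.
- Extra enrolment needed to keep 200 at 25% loss: 267 - 250 = 17 per site.

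**Step 3. Check the base figure of 200**

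For cure rate, assume a one-sample test of a proportion with the normal approximation, null p0 and alternative p1 = p0 - 0.10:

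n = [z_alpha √(p0(1 - p0)) + z_power √(p1(1 - p1))]² / (p0 - p1)²

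- 50% against 40%, two-sided 5%, 80% power: (1.960 x 0.5 + 0.842 x √0.24)² / 0.01 = 193.8, so 194 (204 with continuity correction).
- The same, one-sided 5%: 152.5, so 153 (163 with continuity correction).

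The two-sided version is compatible with a ceiling of 200. That does not prove it was the calculation used. The 200 for egg count reduction comes from simulations whose inputs are not given, so it cannot be recomputed.

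**Step 4. Power at about 187**

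(a) Take 200 as giving exactly 80% and scale by √n: power = Φ[(z_alpha + 0.842) √(187/200) - z_alpha].
- Two-sided: Φ(0.749) = 77.3%.
- One-sided: Φ(0.759) = 77.6%.

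(b) Use the cure-rate test of Step 3: power = Φ[(0.10 √n - z_alpha √(p0(1 - p0))) / √(p1(1 - p1))].

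| Null vs alternative | n | Two-sided 5% | One-sided 5% |
|---|---|---|---|
| 50% vs 40% | 200 | 81.2% | 88.6% |
| 50% vs 40% | 187 | 78.6% | 86.7% |
| 40% vs 30% | 187 | 81.3% | 89.0% |
| 70% vs 60% | 187 | 83.1% | 89.5% |
| 80% vs 70% | 187 | 89.9% | 93.9% |

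In the two-sided case, power is below 80% only for null cure rates of about 44% to 62% (the limits move by about a point according to whether 187.5 is rounded). The minimum is 78.4% at n = 187.

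**The case against.** The strongest reply concerns weight, not arithmetic, and most of it stands.

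- **The 200 is a ceiling.** The protocol says so for both endpoints and ties the largest cure-rate samples to nulls near 50%. Away from that region 187 is enough: 80% against 70% needs only 137 two-sided. This stands, so the shortfall concerns the worst case only.
- **The gap may be smaller than 12 to 13.** Under the assumed two-sided cure-rate test the requirement is 194, which leaves a gap of 194 - 187 = 7, and 194/0.75 = 259. This stands for that endpoint under that assumption. The protocol nevertheless inflated from 200, so 200 is the right figure for checking its sentence.
- **The hypothesis is a drop, so a one-sided test is possible.** With a one-sided 5% test, 187 children still give 86.7% power at 50% against 40%, and the cure-rate shortfall disappears. This also stands. It does not affect the inflation error, which does not depend on sidedness.
- **The target is a minimum.** Sites may enrol more, so 187 is a planning floor rather than the expected yield. But 250 is also the figure called necessary, and nothing in the protocol plans for more.

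A reader might infer that the trial is underpowered, or that every site must recruit 267. The document supports neither. It does not fix the test or its sidedness, the loss of power is a few points in a narrow range of scenarios, and the egg-count power cannot be checked. A reader might also take 78% to 79% as the power at 187. That figure rests on an assumed test and says nothing about egg count reduction. It also relates to children infected with any of the helminths, and the number evaluable for a single species may be smaller.

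**Conclusion.** Wrong as written, and minor. Given the protocol's own inputs, 250 does not preserve 200 evaluable children at 25% loss: it leaves about 187, and 267 would be needed. No other statement in the protocol accounts for 250. This conclusion rests only on reading the non-compliance rate as a fraction of those enrolled, and on non-compliers leaving the analysis, which the exclusion of children without a follow-up stool supports.

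The effect on power is small and conditional: about 77% if 200 gives exactly 80%; for cure rate at 50% against 40%, about 79% or 87% according to sidedness. Nothing in the conduct or analysis of the trial needs to change because of it.

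**What to change.** Rewrite the one sentence that derives 250, in either of two ways:

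1. Keep 250 and state that it tolerates at most 20% loss, since 250 x 0.80 = 200.
2. Keep the 25% and state that 250 yields about 187 evaluable children, slightly below the worst-case 200, and that 267 would be needed to retain 200.

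In both cases, say that the count is of children infected with at least one of the helminths, so the number evaluable for each species may be lower. Do not attach a specific power figure to 187 unless the test and its sidedness are stated with it.

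The cost is one sentence and a slightly less favourable statement of what 250 achieves. No additional enrolment is required.

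### Eligibility and data collection ignore anthelmintic treatment before the first sample or between the two samples, so recent or outside treatment cannot be told apart from MBZ efficacy

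*Protocol*

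**What the plan says.** Under Study design, Primary objective, entry depends on consent, age and a stool sample: "schoolchildren in the target age range group will be recruited and asked to provide a recent stool sample". Treatment then follows for everyone who gave one: "All children providing stool samples will be treated with MBZ single table of 500mg under supervision". The second sample is taken 7 to 14 days later. The only exclusions are "Subjects who are unable to provide a stool sample at follow-up, or who are experiencing a severe concurrent medical condition or have diarrhea", the last of these judged at the first sampling. Treatment history appears nowhere in these rules, and no other section asks for it.

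The same document describes a population in which such treatment is to be expected. Section 1 speaks of "a scale-up of these large-scale treatment programs underway" with albendazole and mebendazole. Section 3.1 says of the sites: "Each of these study sites has a documented history of STH and drug selection pressure". It says of the age group: "School children are normally a major target for regular treatment with anthelminthic".

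Section 3.4 refers the statistical analysis to the publication of the earlier albendazole trial. It does not refer eligibility or data collection there.

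**The concern.** FECR and CR here are before-and-after measures in a single treated group. Anything else that changes the worm population or the egg count is credited to, or charged against, the study dose. There are two routes.

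- **Before the first sample.** If a child recently had a benzimidazole, the worms present at baseline are weighted towards those that survived the same drug class. The study dose then looks weaker than it would in a child not recently treated.
- **Between the samples.** A non-study anthelmintic adds its own effect, and MBZ looks stronger.

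Section 1 gives the reason for monitoring as detecting changes in efficacy that may come from selection of resistant worms. A lower reading caused by a recent round is easily mistaken for that. Without treatment dates the two cannot be separated, and no later analysis plan can recover dates that were never collected.

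**Working it through.** **1. The yardstick.** The protocol is sized for a 10-point drop from about 80% in mean individual egg count reduction, and about 10 points in cure rate, with α = 0.05, power 80% and up to 200 children. The cure-rate figure can be reproduced with a one-sample, two-sided test of a proportion:

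n = [(1.96·√(p0(1−p0)) + 0.842·√(p1(1−p1))) / (p0−p1)]²

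With p0 = 0.50 and p1 = 0.40, n = 194; with 0.55 and 0.45, n = 195. Both agree with up to 200. The egg count simulation cannot be rerun because its variance structure is not given. The sample size is not in dispute here; the 10 points serve only as the scale.

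**2. Treatment before the first sample, egg count reduction.** All mixture figures are assumptions. Suppose worms are of two kinds in equal numbers, survival is a fixed trait of the worm, the earlier round acted like the study dose, there is no reinfection, and egg output follows worm numbers.

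| | Stronger variation | Milder variation |
|---|---|---|
| Chance of removal, two kinds | 95% / 65% | 90% / 70% |
| Removed by a first dose | 0.5×0.95 + 0.5×0.65 = 80% | 0.5×0.90 + 0.5×0.70 = 80% |
| Survivors | 0.025 : 0.175 = 12.5% : 87.5% | 0.05 : 0.15 = 25% : 75% |
| Removed by the study dose | 0.125×0.95 + 0.875×0.65 = 68.75% | 0.25×0.90 + 0.75×0.70 = 75% |
| Fall if all children recently treated | 11.25 points | 5 points |

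The share f of analysed children who were recently treated is not in the documents. On the protocol's own scale, the mean of individual reductions, the fall is f times the last row:

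- f = 30%: 0.30×11.25 = 3.4 points; 0.30×5 = 1.5 points.
- f = 5%: 0.05×11.25 = 0.6 points; 0.05×5 = 0.25 points.

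A group reduction weighted by egg burden dilutes this further. With f = 30%, treated children carrying 20% of the usual burden, and the stronger mixture: (0.7×0.80 + 0.3×0.20×0.6875) / (0.7 + 0.3×0.20) = 0.60125/0.76 = 79.1%, a fall of 0.9 points.

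**3. Treatment before the first sample, cure rate.** If recently treated children have r times the usual cure rate, the fall is CR·f·(1−r). Assume f from 5% to 30% and r from 0.75 to 0.50.

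- CR 50%: 0.50×0.05×0.25 = 0.6 points, up to 0.50×0.30×0.50 = 7.5 points.
- CR 80%: 0.80×0.05×0.25 = 1.0 point, up to 0.80×0.30×0.50 = 12.0 points.

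**4. Treatment between the samples, cure rate.** If a share f receives an outside dose that clears a share c of those otherwise uncured, the rise is (1−CR)·f·c. Assume f from 5% to 30% and c from 30% to 80%.

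- CR 50%: 0.50×0.05×0.30 = 0.75 points, up to 0.50×0.30×0.80 = 12.0 points.
- CR 80%: 0.20×0.05×0.30 = 0.3 points, up to 0.20×0.30×0.80 = 4.8 points.

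The upper ends require 30% of children to receive an outside dose within 7 to 14 days of a supervised study dose. Nothing in the protocol suggests that, so the lower ends are the more credible.

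**The case against.** The strongest reply is that the protocol is silent rather than wrong, and that much is being built on the silence. Several parts of this stand.

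- **Size.** The 11-point fall needs an assumed mixture and a sample in which every child was recently treated. At 30% it is 3.4 points or less.
- **The between-sample route.** The window is short and follows a supervised dose, so the effect is probably small.
- **Direction.** If survival is heritable, a lower reading after a round is partly the signal sought. For cure rate, lower baseline counts against the 50 EPG detection limit could push the result upward. The sign is therefore not certain either.
- **Division of labour.** Analysis sets and displays commonly sit in an SAP, which may exist.

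The last point does not answer the concern. Eligibility and what is asked of each child are fixed at first sampling, and an SAP can use only data that were collected. The uncertainty about size and direction is likewise a reason to record treatment history, not a reason to omit it.

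A reader might also infer more than the text supports. Section 3.1 does not say the sites were chosen for drug pressure: six come from the 2009 study and one is a replacement. It calls schoolchildren a usual target of treatment in general and does not say that these schools were under regular treatment. The protocol does not require a child treated between samples to stay in the efficacy analysis; it does not address the case. Comparing sites is not a stated objective, so confounding of site differences with the deworming calendar defeats no declared aim.

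**Conclusion.** The gap is real and worth closing, but it does not by itself invalidate the study. As written, the study cannot distinguish recent carry-over or outside treatment from MBZ efficacy, in a setting the protocol itself describes as exposed to these drugs. The size is unknown. For egg count reduction, the illustrative fall is 5 to 11 points if all sampled children were recently treated and about 1.5 to 3.4 points if 30% were, against the 10-point drop the study is sized to detect. It is negligible if few were treated. These figures rest on the assumed worm mixtures, no reinfection, and assumed shares of treated children.

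It would be tempting to say that the bias equals the whole target signal. The documents do not support that: it holds only at the extreme of the assumed range.

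**What to change.** Add to the Primary objective text under Study design:

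1. At first sampling, record the date and drug of each child's last anthelmintic, from the school or programme log or from parent report, including when it is unknown.
2. At follow-up, record any non-study anthelmintic taken since the study dose. Leave those children out of the main FECR and CR analysis.
3. Present FECR and CR by time since last treatment as a sensitivity display.

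The cost is one or two questions per child, some recall error where no log exists, and a few exclusions. No change to treatment or to programme scheduling is proposed.
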